#### Data collection

Upon consent for participation each subject will be invited for three visits: 3, 6 and 12 months post-injury for data collection. This timeframe is chosen based on the recommendations of the AAOS enabling return to work/sport within 3–6 months and the recovery phase of ATR management starting at 3 months post-injury.

### Measurements

Table 1 presents an overview of the specific data collected.

**Table 1 Tab1:** Measurements per visit

Data Category	Outcome measure/tool^a^	Month 3	Month 6	Month 12
Demographic and Lifestyle	Baseline questionnaire	X		
Medical	Medical file	X	X	X
PROMs	ATRS-NL^b^ questionnaire	X	X	X
	EQ-5D-5 L questionnaire	X	X	X
	OSTRC^c^-Overuse questionnaire	X	X	X
	I-PRRS^d^	X	X	X
	TSK^e^	X	X	X
	Expectations, motivations and satisfaction questionnaire	X	X (only satisfaction and motivation)	X (only satisfaction and motivation)
	Reasons for not RTS		X	X
Physical tests	Heel-rise test	X	X	X
	Ankle dorsiflexion ROM^f^	X	X	X
	Tendon length	X	X	X
	Single leg hop for distance			X
Imaging	UTC^g^	X	X	X
Economic questionnaires	iPCQ^h^	X	X	X
	iMCQ^j^	X	X	X

^a^ A detailed description of the specific outcome measures/tools is given in the subsection measurements. ^b^. Dutch version of the Achilles Tendon Total Rupture Score ^c^. Oslo Sports Trauma Research Center ^d^. Injury Psycological Readiness to Return to Sport ^e^ Tampa Scale of Kinesiophobia ^f^. Range of motion ^g^. Ultrasound Tissue Characterization ^h^. Productivity Cost Questionnaire ^j^. Medical Consumption Questionnaire

#### Demographic and lifestyle data

A baseline questionnaire concerning personal subject data was constructed for specific use in this study. The items in this questionnaire concern biographical information (age), anthropometrics (height, weight), lifestyle factors (smoking, (level of) physical activity, work, urban/rural inhabitant), personal and family medical history including injuries and tendon complaints, injury (etiology, extent, and symptoms) and management factors during rehabilitation (physiotherapy).

#### Medical data

The patients’ medical files will be inspected at baseline for medical history, medication, injury (etiology and extent (gap-size)) and ATR management (treatment delay, surgical or non-surgical treatment and methods, methods and length of rehabilitation, imaging applied) data. Additionally, the medical status will be monitored throughout the study period for information on injury, treatment and complications if applicable.

#### PROMs

The Achilles Tendon Total Rupture Score (ATRS) is a questionnaire used to measure outcome related to symptoms and physical activity after treatment in patients with an ATR [41]. It consists of ten questions each concerning ten points. This instrument is a valid and reliable method of measuring outcome in ATR patients [41]. It is a self-administered instrument with high clinical applicability, and the score can be used to measure the outcome related to symptoms and physical activity, after treatment in patients with a ATR. In this study the Dutch version will be used (ATRS-NL) which is found to be valid and reliable [42]. In the Dutch version the maximum score (=maximum disability) =100. This measurement will serve as the primary outcome in the analyses.

The Dutch version of the EQ-5D-5L is the most commonly used generic questionnaire to measure quality of life. It encompasses physical, mental, emotional and social functioning. This questionnaire is used to make decisions in cost-effectiveness analyses [43]. The EQ-5D-5 L is scored on a 5-point Likert scale. The result score is a 5-number index score, reflecting the individual’s health-profile. This score can be converted to a total score between 0 (death) and 1 (completely healthy).

The OSTRC Overuse Injury Questionnaire is a 5-question tool used to estimate the burden of injury with respect to RTS, specifically with respect to knee, shoulder or lower back injury. This questionnaire has been found valid [44]. We have modified the Dutch version of this questionnaire to pertain to Achilles tendon injury. This questionnaire will be used to determine the effect of injury on the RTS.

The Injury Psychological Readiness Return to Sport (I-PRRS) Questionnaire assesses an athlete’s psychological readiness to RTS after injury [45]. The I-PRRS is a valid and reliable tool for measuring psychological readiness to RTS. The questionnaire consists of six items that are each scored on a 100-point scale. The total score ranges from 0 to 60 and consists of the sum the six items, divided by 10. A higher score implies greater confidence to RTS. We translated the I-PRRS into Dutch following international guidelines [46, 47].

The Tampa Scale of Kinesiophobia (TSK) measures fear of re-injury due to movement and physical activity. It contains 17 items scored on a four-point Likert scale regarding the subjective experience of the injury and physical activity. The sum of the items results in a score between 17 and 68, where 68 indicates a high level of fear [48]. For this study, the modified Dutch version, adapted for tendon injuries will be used [49]. This questionnaire has been validated in Dutch for measurement of fear of movement/reininjury, although not in an ATR population [49].

A questionnaire concerning expectations, motivation and satisfaction with regard to RTS was constructed. This questionnaire contains 15 questions divided over three dimensions: Expectations (9 questions), Motivation (3 questions) and Satisfaction (3 questions) based on the questionnaire by Sonneson & Ardern (2016) [50]. The questionnaire was designed specifically for use in this study.

A questionnaire concerning reasons for not RTS will be administered. The questionnaire consists of a ranking scale used in prior psychosocial RTS studies after Anterior Cruciate Ligament (ACL) injury [51]. The scale has been translated to Dutch and we modified it to pertain to Achilles tendon injury. The scale was based on the previous reported data on RTS after ACL injury [51]. Patients who reported that they had not returned to their preinjury activity were asked to rank the following reasons for not returning from most important to least important: ‘poor tendon function’, ‘do not trust the tendon, ‘fear getting a new injury’, ‘team or training has changed’, ‘family commitments’, ‘work commitments’ and ‘other reasons’.

#### Physical tests

Endurance will be assessed with the single leg heel-rise test. This test is a reliable measure of endurance in patients after ATR [52]. With this test patients are instructed to stand on one foot on a 60 degree incline board and perform as many heel-rises as possible. Figure 1 shows the heel-rise test setup. Patients are allowed to have 2 fingertips per hand against the wall for balance, and will perform the rises at a rate of 30 heel rises per minute as guided by a metronome. For each heel-rise they are instructed to go as high as possible and then lower the heel to the starting position. The test will be terminated when the patients stop, cannot maintain the frequency, or cannot perform a proper heel rise [53]. The heel-rise count of the injured foot will be compared to the contralateral (uninjured) foot. The outcome is calculated as the percentage of the heel-rise test count of the ATR-affected side compared to the contralateral (uninjured) limb. The unaffected side is evaluated first.

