**Fig. 1 Fig1:**
[figure not shown]
Heel-rise test

The tendon length of both the injured and uninjured Achilles tendon will be measured by determining the resting tension on the ankle (the resting plantarflexion with the patients foot prone on an examination table with the feet hanging over the edge). The degree of plantarflexion represents the tendon length [54]. Resting plantarflexion will be measured by using goniometer placed along the lateral border of the foot as described by Ecker et al. [54], this method has been described previously and determined to correlate to muscle strength. The outcome concerns the difference in resting prone plantarflexion between the injured and contralateral foot.

Maximum standing dorsiflexion range of motion (ROM) will be measured with a goniometer with the patient standing. This method has been shown to have good reliability [53, 55]. Care will be taken to place the foot in a subtalarneutral position. The proximal arm of the goniometer will be aligned with the midline of the fibula, the fulcrum with the lateral malleolus, and the distal arm parallel to the fifth metatarsal. The ROM will be compared to the contralateral (healthy) foot.

The entire lower extremity will be tested with the single leg hop for distance. In this test the patient is instructed to stand on one leg and to hop once as far forward as possible, landing only on the same leg. The single leg hop is a reliable test for the function of the lower extremity [56]. The distance from the tip of the patient’s great toe at the starting position to the tip of the patient’s great toe in the landing position is recorded with a tape measure. This test will only be performed at 12 months post-injury. Each leg will be tested three times, and the mean distance hopped over the three repetitions is used for the analysis. The unaffected side is evaluated first.

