### Statistical analysis

IBM SPSS Statistics for Windows software (Version 23.0, Armonk, NY: IBM Corp.) will be used for all statistical data analyses. Descriptive statistics (frequencies, means and standard deviations, etc.) will be used to describe all data. Spearman’s correlation coefficients will be used to describe association between data. Statistical significance is defined as *P* < 0.05.

The following are the planned statistical analyses *per aim*:
*Primary aim:*
Generalized estimating equations (GEEs) will be conducted to assess the outcomes over time: 3, 6, and 12 months.

*Secondary aim:*
Linear regression analyses will be performed to assess factors predictive of Achilles tendon function. First, univariate analysis will be performed as a hypothesis-generating analysis model with ATRS-NL score (0–100) as dependent variable and a predicting factor as independent factor. Factors showing a relation with the outcome measure with a *p*-value < 0.20 will be included in a multiple linear regression analysis. Additionally, binary logistic regression will be used to determine the factors associated with returning to the pre-injury sport or recreational activity. Return to the pre-injury activity (yes or no) is the outcome variable.The Incremental Cost-effectiveness Ratio (ICER) (=Δ Cost of treatment/Δ Effect of treatment) associated with each unique treatment modality will be calculated. The ICER is calculated by taking the difference in costs associated with each possible treatment modality and its alternative (e.g. physiotherapy vs. no physiotherapy) and dividing by the difference in effect. Costs are calculated by adding the direct (e.g. cost of treatment from iMCQ questionnaire) and indirect (e.g. loss of work, from iPCQ questionnaire) costs associated with each possible treatment. Effect consists of the EQ-5D-5 L and/or ATRS-NL outcomes. The cost-effectiveness of ATR management options will herewith be determined at 3, 6, and 12 months post injury.

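### The three repeated physical tests are scored only against the other leg, which eligibility does not guarantee is sound; the injured-side values should be analysed beside the index

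*Protocol article*

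**What the plan says.** Under Methods, Physical tests, the Protocol article defines three measures by comparison with the opposite limb.

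- Heel-rise: "The outcome is calculated as the percentage of the heel-rise test count of the ATR-affected side compared to the contralateral (uninjured) limb".
- Tendon length, measured as resting plantarflexion: "The outcome concerns the difference in resting prone plantarflexion between the injured and contralateral foot".
- Standing dorsiflexion: "The ROM will be compared to the contralateral (healthy) foot". Whether this comparison is a ratio or a difference is not stated.

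Table 1 schedules all three at months 3, 6 and 12. For the primary aim, the Statistical analysis section states: "Generalized estimating equations (GEEs) will be conducted to assess the outcomes over time: 3, 6, and 12 months".

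The inclusion criteria (Participants and setting) require adult age and a clinically diagnosed rupture treated at one of the three hospitals. The exclusions concern written Dutch and the ability to do the tests and questionnaires. Neither list mentions the other leg. The baseline questionnaire does cover "personal and family medical history including injuries and tendon complaints", and the medical file is inspected for medical history, but the article links neither source to the side-to-side comparison.

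The remaining outcomes do not depend on the other leg. Of the ATRS-NL the article says: "This measurement will serve as the primary outcome in the analyses". UTC is reported as shares of four echo-types. For the hop test, "Each leg will be tested three times, and the mean distance hopped over the three repetitions is used for the analysis", with no ratio stated, and it takes place at one visit: "This test will only be performed at 12 months post-injury".

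**The concern.** A side-to-side index reads as recovery of the injured leg only if the reference leg is sound and does not change. The article labels the other leg uninjured for heel-rise and healthy for dorsiflexion, but admits patients for whom that may be untrue: those with a previous contralateral rupture, contralateral tendon complaints, or rupture on both sides. In such a patient the heel-rise percentage can look near normal although both legs are weak. With bilateral rupture the stated reference does not exist.

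The second issue is change over time. Heel-rise is an endurance count, and the Data collection section places return to work and sport between months 3 and 6, inside the measurement window. The other leg's endurance may therefore change between visits. If its count is renewed each time, the slope estimated by the GEE combines change in both legs. At stake is how the physical-test recovery curves are interpreted, in a study whose primary aim is to describe recovery.

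**Working it through.** **Inputs.** The definitions and schedule are those set out above. The article gives no heel-rise counts, no standard deviations and no prevalence of contralateral injury, so there is no stated figure to reproduce. All counts and shares below are assumptions used to show direction and range.

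**Step 1: algebra.** Let I and C be the injured-side and contralateral values at a visit.

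- Ratio (heel-rise): R = 100 × I / C. The relative change in R is the relative change in I divided by the relative change in C.
- Difference (resting plantarflexion): D = I − C, so change in D = change in I − change in C.

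A stable but abnormal C therefore shifts the level of both indices. It leaves the relative change in R, and the change in D, as they were. A changing C alters the slope of both.

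**Step 2: a moving reference (heel-rise, assumed injured-side counts 10, 18, 24).**

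| Other leg at months 3, 6, 12 | R at months 3, 6, 12 | Gain, points |
|---|---|---|
| 30, 30, 30 | 33.3%, 60.0%, 80.0% | 46.7 |
| 30, 31.5, 33 (up 10%) | 33.3%, 57.1%, 72.7% | 39.4 |
| 30, 33, 36 (up 20%) | 33.3%, 54.5%, 66.7% | 33.3 |
| 30, 28.5, 27 (down 10%) | 33.3%, 63.2%, 88.9% | 55.6 |

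The injured leg is identical in every row. If it instead stays flat at 20, R still moves: from 20/30 = 66.7% to 20/36 = 55.6% when the other leg rises by 20%, or to 20/27 = 74.1% when it falls by 10%.

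**Step 3: an impaired reference.** With the same injured-side counts and the other leg at 20 throughout, R is 50%, 90% and 120%. The last value suggests better than full recovery in a patient impaired on both sides. The relative change, 120/50 = 2.4, equals 80/33.3 = 2.4 with a sound reference, but the gain in points is 70.0 rather than 46.7.

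**Step 4: effect on the cohort mean.** If a share q of patients has a contralateral deficit d, a mean of 80% becomes 80 × [(1 − q) + q/(1 − d)].

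- q = 0.02, d = 0.20: 80 × (0.98 + 0.025) = 80.4%.
- q = 0.10, d = 1/3: 80 × (0.90 + 0.15) = 84.0%.

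Over this assumed range the mean is inflated by 0.4 to 4.0 points. The effect is modest on average and large in the individual patient.

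**The case against.** The best defence is that side-to-side indices are a legitimate and common choice. A same-visit reference offsets influences shared by both legs, such as general fitness, motivation and familiarity with the test, and a raw injured-side count loses that control. This stands, and it is a reason to keep the index and add to it rather than replace it.

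It is also fair that the article is a condensed account and that a rule for the few patients with contralateral injury could sit in a full protocol or SAP that is not shown. But the outcome definitions are given in the article itself. Applied as written, they score these patients against an impaired leg.

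A reader might infer more than the text supports:

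- **That functional recovery as a whole is scored only against the other leg.** It is not. The ATRS-NL is the primary outcome and the dependent variable in the linear regression for tendon function, and it has no limb reference. UTC has none either, and none is stated for the hop.
- **That the plan assumes a stable reference leg and re-measures it at each visit.** Neither is stated. Re-testing is the natural reading of Table 1 and of the instruction to evaluate the unaffected side first, but it remains an inference.
- **That deconditioning distorts all three tests.** The argument fits an endurance count. Nothing in the article suggests that contralateral resting plantarflexion or dorsiflexion drifts between months 3 and 12.

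**Conclusion.** The point holds for three secondary measures. Heel-rise, resting plantarflexion and dorsiflexion are the only physical tests repeated over time, all are defined relative to the other leg, and eligibility does not ensure that this leg is sound. For heel-rise, the GEE slope also reflects change in the other leg, provided that leg is re-tested at each visit.

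The size cannot be computed from the document. Under the assumed counts, a 10% fall to a 20% rise in the other leg moves the heel-rise gain between 55.6 and 33.3 points around a true-reference value of 46.7. An assumed 2% to 10% of patients with a 20% to 33% contralateral deficit raises a mean of 80% to between 80.4% and 84.0%. The ATRS-NL analyses are untouched. This is a worthwhile, low-cost improvement to secondary outcomes and does not threaten the main result.

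**What to change.** Keep the side-to-side index and make three additions to the Physical tests and Statistical analysis sections.

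1. Enter the injured-side value (heel-rise count, degrees of resting plantarflexion, degrees of dorsiflexion) as an outcome in the GEE beside the index.
2. Report the contralateral values at each visit, so that a reader can see which leg moved.
3. Compute the index only in patients without previous or current contralateral Achilles injury, identified from the baseline questionnaire and medical file. The others contribute injured-side values only. Confirm first that the side of any earlier injury is recorded, because the article does not mention side.

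Do not replace the same-visit reference with a fixed one. A month-12 value is missing for patients who leave before then, and the article cites dropout of 10–20% in similar studies. The highest value over the visits picks up upward measurement noise and depends on how many visits were attended.

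Cost: no extra test or visit if both legs are tested each time as the procedure suggests, and a small addition to the questionnaire or file extraction if side is not yet captured. A few patients leave the index analysis, and each test needs a second presentation.

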**Fig. 1 Fig1:**
[figure not shown]
Heel-rise test

The tendon length of both the injured and uninjured Achilles tendon will be measured by determining the resting tension on the ankle (the resting plantarflexion with the patients foot prone on an examination table with the feet hanging over the edge). The degree of plantarflexion represents the tendon length [54]. Resting plantarflexion will be measured by using goniometer placed along the lateral border of the foot as described by Ecker et al. [54], this method has been described previously and determined to correlate to muscle strength. The outcome concerns the difference in resting prone plantarflexion between the injured and contralateral foot.

Maximum standing dorsiflexion range of motion (ROM) will be measured with a goniometer with the patient standing. This method has been shown to have good reliability [53, 55]. Care will be taken to place the foot in a subtalarneutral position. The proximal arm of the goniometer will be aligned with the midline of the fibula, the fulcrum with the lateral malleolus, and the distal arm parallel to the fifth metatarsal. The ROM will be compared to the contralateral (healthy) foot.

The entire lower extremity will be tested with the single leg hop for distance. In this test the patient is instructed to stand on one leg and to hop once as far forward as possible, landing only on the same leg. The single leg hop is a reliable test for the function of the lower extremity [56]. The distance from the tip of the patient’s great toe at the starting position to the tip of the patient’s great toe in the landing position is recorded with a tape measure. This test will only be performed at 12 months post-injury. Each leg will be tested three times, and the mean distance hopped over the three repetitions is used for the analysis. The unaffected side is evaluated first.

#### Imaging

Ultrasound Tissue Characterization (UTC) is a novel device that can tomographically visualise and accurately quantify tendon structure in three planes. The device has a 7–10 mHZ transducer that moves automatically over tendons and makes transverse recordings over regular intervals of 0.2 mm (Fig. 2) [57]. Operator-dependent variables like transducer tilt, angle, gain and depth are standardized in this scanning method. Tendon structure is quantified via the analysis of the Achilles tendon based on echo-type stability. UTC quantifies tendon structure in four distinct types (I-IV) depending on the amount of fibrillar disorganization and tendon integrity. Echo-type I is the most stable echo pattern and echo-type IV is the least stable echo pattern [57]. The entire tendon will be analyzed. The outcome consists of the percentage of the four different echo-types. This quantification of tendon structure provides the possibility to monitor subtle changes [57]. The UTC has not been used ATR in patients, but has shown potential as a monitoring device in the evaluation of tendinopathy patients and assessing the quality of (Achilles) tendon structure [57].

**Fig. 2 Fig2:**
[figure not shown]
UTC device (probe and tracker) [59]

#### Economic questionnaires

For productivity costs the the institute for Medical Technology Assessment (iMTA) Productivity Cost Questionnaire (iPCQ) will be administered. The iPCQ is a specially constructed Dutch questionnaire designed to measure the indirect costs associated with treatment. It contains three modules (absenteism, presenteeism and productivity losses related to and unpaid work) designed to measure all of the indirect costs associated with medical treatment [58].

For direct medical costs the iMTA Medical Consumption Questionnaire (iMCQ) will be administered. The iMCQ is a specially constructed Dutch questionnaire designed to measure the direct costs associated with treatment. The questions concern ambulance and emerency room use, visits to general practice and the hospital and use of physiotherapty and alternative (homeopathy, acupuncture, e.g.) care. The iMTA costing tool handbook will be used to to collect reference value for treatment costs in the Netherlands.

